# The Effectiveness of a Computer Game-Based Rehabilitation Platform for Children With Cerebral Palsy: Protocol for a Randomized Clinical Trial

**DOI:** 10.2196/resprot.6846

**Published:** 2017-05-18

**Keywords:** repetitive task practice, cerebral palsy, fine motor skills, game-based exercise, randomized controlled trial, upper extremity function

## Abstract

**Background:**

It is difficult to engage young children with cerebral palsy (CP) in repetitive, tedious therapy. As such, there is a need for innovative approaches and tools to motivate these children. We developed the low-cost, computer game-based rehabilitation platform CGR that combines fine manipulation and gross movement exercises with attention and planning game activities appropriate for young children with CP.

**Objective:**

The objective of this study is to provide evidence of the therapeutic value of CGR to improve upper extremity (UE) motor function for children with CP.

**Methods:**

This randomized controlled, single-blind, clinical trial with an active control arm will be conducted at 4 sites. Children diagnosed with CP between the ages of 4 and 10 years old with moderate UE impairments and fine motor control abnormalities will be recruited.

**Results:**

We will test the difference between experimental and control groups using the Quality of Upper Extremity Skills Test (QUEST) and Peabody Developmental Motor Scales, Second Edition (PDMS-2) outcome measures. The parents of the children and the therapist experiences with the interventions and tools will be explored using semi-structured interviews using the qualitative description approach.

**Conclusions:**

This research protocol, if effective, will provide evidence for the therapeutic value and feasibility of CGR in the pediatric rehabilitation of UE function.

**Trial Registration:**

Clinicaltrials.gov NCT02728375; http:https://clinicaltrials.gov/ct2/show/NCT02728375 (Archived by WebCite at http://www.webcitation.org/6qDjvszvh)

## Introduction

### Background and Rationale

Canada and India face a growing population of children with cerebral palsy (CP), with the condition occurring in 2 to 4 of every 1000 live births in North America and India, respectively [1-3]. Children with CP have deficits in fine and gross motor skills, often with co-occurring deficits in visual-spatial processing skills [4-6]. The ability to perform functional tasks with the upper extremities (UEs) is an important predictor of success in daily activities and participation in school, leisure, and social activities [7]. Therapy programs designed to improve UE motor and visual-spatial processing skills must strive to maximize neurodevelopmental capacities and prevent secondary disabilities [8,9].

There are different approaches to therapy for children with CP [10-17]. The effectiveness of these programs is proportional to the intensity and amount of training and the task-specificity of the exercise regime [18-21]. For example, constraint-induced movement therapy (CIMT) and hand-arm bimanual intensive therapy (HABIT) are promising rehabilitation programs for restoration of hand-arm function. These treatment approaches stress that both functional demands and repetitive intensive training are important in the rehabilitation of fine motor skills and to restore functional skills. Typically CIMT needs administration of 6 hours a day and the child can use only the affected arm, making bimanual activities impossible to perform. There is growing evidence to support the idea of activity-dependent central nervous system (CNS) plasticity [22]. In addition, the notion is emerging that neural reorganization reflects learning achieved through generating real experiences, applying focused attention, simulating close-to-normal movements, and repetition [23]. However, it is difficult to engage children with CP in therapy for long periods of time and sustain motivation for the intense repetitive task practices. Thus, there is a need for innovative and cost-effective therapeutic approaches and tools that motivate children with CP to complete long-term neurorehabilitation programs and that provide opportunities to improve neurodevelopmental outcomes.

Parents and clinicians rate motivation as the most influential personal characteristic for adherence to therapy and for determining motor and functional outcomes in children with CP [24]. An emerging, promising approach to engaging children in therapy is to incorporate computer games in which a range of learning elements with interactive cognitive challenges help children to positively engage in activities. Studies have provided evidence of the benefits of video games in rehabilitation training and show that well-designed interactive games can improve players' motor skills and visual-spatial processing skills [24-30].

For this purpose, we developed the low-cost, computer-aided, game-based rehabilitation and learning platform CGR [31-37]. CGR combines fine or gross motor exercises and visual-spatial cognitive activities appropriate for children with CP in a game-based format. A motion detecting “Therapy Mouse” (Mobility Research, AZ) will be used as the computer game controller. It is a miniature and wireless plug-n-play computer interface device, which contains firmware and inertial sensors that allow physical motion, specifically instantaneous position, to be translated and interpreted as a standard motion of a Universal Serial Bus (USB) mouse, and which has high fidelity and responsiveness. Because the miniature motion mouse can be easily attached with Velcro to many objects, this approach provides a highly flexible therapy tool applied to fine or gross UE motor skills. Many objects with varied sizes, shapes, weights, surface properties, and functional demands can be used for exercise and for practicing a variety of gross or fine motor skills. Importantly, when the motion mouse is attached to the chosen object fun computer games can be played [8,28,31,36-37]. As CGR allows handling and manipulation of many objects (ie, ones commonly used in daily activities), activity goals can be imbedded in the therapy program. Many inexpensive modern games, “exergames,” and brain fitness games now exist that are visually rich, fun, and engaging, include a variety of visual-spatial tasks, and require choice and other planning type activities. Performing goal-directed manipulation tasks through engaging and guided repetition creates experiences crucial to improving the brain's ability to learn [10,37].

### Study Objectives

A randomized controlled trial (RCT) with an intention-to-treat is proposed to evaluate the effectiveness of the game-based rehabilitation program on fine manual dexterity, upper limb motor skills, and visual-spatial cognitive functions in children aged 4 to 10 years old diagnosed with CP. This single-blind randomized clinical trial with an active control arm will be conducted at 4 sites. Two groups of children will be examined: one group will receive the experimental game-based program and the other group will receive usual therapy (see Multimedia Appendix 1). The first hypothesis is that an engaging, game-based UE exercise regime will result in greater improvements in hand-arm function as compared to the usual outpatient physical therapy program. The second hypothesis is that the UE exercise program, which uses computer games having a variety of visual-spatial activities, will result in greater improvements in visuospatial cognitive functions as compared to the usual outpatient physical therapy program.

### Study Design

This study will evaluate the feasibility of the procedures such as recruitment, intervention delivery, participant retention, and measurement tools. Semi-structured interviews will be conducted with the parents of the children and with the treating therapists. The broad research questions are: “what were the experiences of the study participants with the game-based and current therapy programs, and on what context were the experiences based?” The qualitative findings of participant's and therapists' experiences will help to identify (1) perceived exercise benefits; (2) difficulties with the exercises and using the technologies; (3) engagement and motivational value of the computer games; (4) personal and environmental factors that influenced doing the exercises; and (5) recommendations and modifications for improving the exercise programs.

## Methods

### Study Setting

This randomized controlled, single-blind clinical trial with an active control arm will be conducted at the following 4 sites: (1) University of Manitoba and Rehabilitation Centre for Children at the Special Services for Children and Youth (SSCY) Centre (Drs [name], [name], [name], and [name], Winnipeg, Manitoba, Canada); (2) SDM College of Physiotherapy, Dharwad in collaboration with Usha's School for Exceptional Children, Hubli (Drs [name], [name], [name], and [name], Karnataka, India); (3) Christian Medical College (Drs [name], [name], and [name], Ludhiana, Punjab, India); and (4) Kasturba Medical College ([name], Mangalore, Karnataka, India).

### Inclusion Criteria

Children diagnosed with CP (N=140) between the ages of 4 and 10 years old with moderate UE impairments and fine motor control abnormalities will be recruited. The following screening tools will be used: (1) Manual Ability Classification System (MACS), level 2 to 3 [38]; (2) Gross Motor Function Classification Scale (GMFCS), levels 2 to 4 [39]; (3) Ashworth scale of spasticity in wrist and fingers, level 0 to 1+ [40]; and (4) the pediatric version of the Mini-Mental State Examination assessment scale, level 17 and above. This will be used to the screen level of cognitive function. For each site, we will use a permuted block randomization scheme stratified by age and level of impairment as measured by the MACS and GMFCS [41].

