### Procedures and Interventions

Ethical approval was obtained from the health research ethics boards of each site. For each site a permuted block randomization scheme will be used and stratified by age where 4- to 6-year-olds will be one subgroup and 6- to10-year-olds will be the other subgroup. Each program will take 16 weeks, with 3 45-minute sessions per week. A workshop and uniform training program will be organized at SDM College of Physiotherapy, Dharwad, India for physiotherapists who will provide the assessment and the 2 intervention programs. This will be attended by [name] and [name] who will organize and coordinate the therapy program. The 2 intervention groups will be treated in all 4 locations limiting biases like contamination. The therapists conducting the assessments will be blinded to group assignment.

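### The randomisation strata are described in two different ways, and 6-year-olds fall in both age groups, so the allocation lists cannot be built uniquely from the text

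*Protocol article*

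**What the plan says.** The protocol article describes the randomisation twice.

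- **Methods, Inclusion Criteria:** at each site, "we will use a permuted block randomization scheme stratified by age and level of impairment as measured by the MACS and GMFCS". The same section sets the eligible ranges: children "between the ages of 4 and 10 years old", "Manual Ability Classification System (MACS), level 2 to 3" and "Gross Motor Function Classification Scale (GMFCS), levels 2 to 4".
- **Methods, Procedures and Interventions:** "For each site a permuted block randomization scheme will be used and stratified by age". The age groups follow: "4- to 6-year-olds will be one subgroup and 6- to10-year-olds will be the other subgroup". MACS, GMFCS and impairment are not mentioned as strata here.

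The Results section specifies the analysis. It is an ANCOVA of the post-intervention score with the pre-intervention score and group as its only terms. Site, age, MACS and GMFCS do not appear. The same section plans 140 children randomised in equal numbers, and Study Setting lists four sites.

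**The concern.** The two descriptions name different sets of factors for what is plainly the same procedure. A person preparing the lists from this text would have to choose between them. That person would also have to decide, without guidance, where a 6-year-old goes. Age is the one factor that both descriptions share, and it is the one whose categories overlap.

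At stake is a single, reproducible allocation rule across four sites in two countries. A reader also needs to know which factors constrained the randomisation in order to judge whether the analysis should carry them. As written, the analysis model carries none.

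**Working it through.** **1. The plan's own figure.** Results gives 128 analysed children for a difference of 10, SD 25, baseline-to-final correlation 0.6, 80% power and 5% alpha.
- Residual SD = 25 × √(1 − 0.6²) = 25 × 0.8 = 20.
- The normal approximation (two-sided) gives 63 per arm, 126 in total.
- The noncentral t calculation with N − 3 degrees of freedom gives 128, power 0.801.

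The figure reproduces. The sample size is not at issue here.

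**2. The two descriptions side by side.**

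| | Inclusion Criteria | Procedures and Interventions |
|---|---|---|
| Method | Permuted blocks, per site | Permuted blocks, per site |
| Age | Yes, groups not given | Yes, 4 to 6 and 6 to 10 |
| Impairment (MACS, GMFCS) | Yes, categories not given | Not named |

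**3. The age overlap.** A child aged 6 is inside the eligible range and inside both groups. The age distribution is not given. Assume that completed years of age are equally common:
- ages 4 to 10 inclusive: 140 / 7 = 20 children aged 6;
- ages 4 to 9 only: 140 / 6 ≈ 23 children aged 6.

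**4. How far apart the two schemes are.**

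| Factors crossed | Cells | Children per cell |
|---|---|---|
| Site × age | 4 × 2 = 8 | 140 / 8 = 17.5 |
| Site × age × MACS (2 levels) | 16 | 140 / 16 = 8.75 |
| Site × age × GMFCS (3 levels) | 24 | 140 / 24 = 5.8 |
| Site × age × MACS × GMFCS | 4 × 2 × 2 × 3 = 48 | 140 / 48 = 2.9 |

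The last row assumes that each eligible level is a separate category. The article does not say so, and one combined two-level impairment grouping would give 4 × 2 × 2 = 16 cells.

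**5. What the cell count does to balance.** I simulated 140 children with equal cell probabilities. Both those probabilities and the block size of 4 are assumptions. Entries are mean absolute differences between arms, in children:

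| | Overall | Within one MACS level | Within one GMFCS level |
|---|---|---|---|
| 8 cells | 1.9 | 4.8 | 4.6 |
| 48 cells | 5.2 | 3.6 | 3.0 |
| Simple randomisation | about 9.5 | 6.7 | 5.6 |

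With 48 cells, about 67% of cells hold fewer than 4 children, and the 95th percentile of the overall difference is 12. With blocks of 6 these become 93% and 16. So the 48-cell scheme is looser on overall arm sizes than the 8-cell scheme but tighter on MACS and GMFCS. Both do better than no stratification.

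**6. What a 12-child difference costs.** A 76/64 split carries the information of 4 × 76 × 64 / 140 = 139 children split equally, a loss of under 1%.

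**The case against.** The strongest reply is that the two sentences can be harmonised. The first lists the factors, and the second only defines the age cut. The second sentence never says that age is the sole factor. This is a reasonable reading, and it may be what the authors meant. But the second sentence restates the whole per-site scheme without referring back, and the age overlap survives the reading. One could also take 4 to 6 as ending at the sixth birthday. The wording speaks of 6-year-olds in both groups, however, so the text does not settle the matter.

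Three stronger conclusions are tempting, and the documents do not support them.

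- **That the impairment strata are too many for blocking to work.** The 48-cell count and the block size are not in the article. Even if both are granted, 48 cells still roughly halves the overall imbalance of simple randomisation, and it balances MACS and GMFCS better than 8 cells do.
- **That staff could steer 6-year-olds between lists.** This requires knowledge of upcoming assignments and control of the list. The article does not describe who holds the lists or how allocation is concealed. An article commonly leaves that to the full protocol, so no weakness can be inferred.
- **That the comparison is biased or underpowered.** Allocation remains random and 1:1 under either description, and the power effect is negligible.

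It is also fair to say that removing MACS and GMFCS from the strata would be a trade-off and not a correction.

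**Conclusion.** The point holds as a defect of specification. The two descriptions differ in their factors. The age groups share the 6-year-olds, and nothing in the article resolves either matter. The allocation lists therefore cannot be derived uniquely from the text. The overlap alone is enough for that conclusion and rests on no assumption. Only its size does: about 20 to 23 of 140 children if completed years of age are equally common.

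The ANCOVA as stated includes none of the stratification factors under either description. An analysis plan not shown here may extend it, but the model given in the article does not reflect the randomisation.

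The sparse-cell calculation is a conditional note only. If every eligible MACS and GMFCS level were its own category, there would be up to 48 cells with about 2.9 children each. Severity is should-fix: the correction is needed for a reproducible design, but no bias or material loss of power has been shown.

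**What to change.** 1. State one identical set of stratification factors, with the categories of each, under both Inclusion Criteria and Procedures and Interventions.
2. Make the age groups mutually exclusive, for example under 6.0 years versus 6.0 years and over at randomisation.
3. Add the factors to the ANCOVA: site, age group and, whether or not they remain strata, MACS and GMFCS. As categories these use 3 + 1 + 1 + 2 = 7 degrees of freedom. That leaves 125 − 7 = 118 residual degrees of freedom at 128 analysed children.
4. If allocation lists already exist, do not rebuild them. State which factors and which age cut they used, and correct the description that differs.
5. If MACS and GMFCS stay as strata, consider a coarser impairment grouping to limit the number of cells. If they are dropped, say that they are handled by adjustment instead, and accept somewhat looser balance on them by design.

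The cost is a paragraph of text and one line in the analysis model, plus new lists only if enrolment has not begun. MACS and GMFCS are already collected at screening, so no extra data are needed.

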### Exclusion Criteria

Exclusion criteria for the study will be (1) visual or auditory impairment such that they cannot see and interact with the video games; (2) secondary orthopedic complications due to neurodegenerative disease (NDD) or as a result of surgery to the upper limb that may have caused permanent changes in upper limb musculoskeletal structure; (3) recent Botulinum toxin therapy (less than 6 months); (4) seizures, or (5) complex communication disorders.

### Procedures and Interventions

Ethical approval was obtained from the health research ethics boards of each site. For each site a permuted block randomization scheme will be used and stratified by age where 4- to 6-year-olds will be one subgroup and 6- to10-year-olds will be the other subgroup. Each program will take 16 weeks, with 3 45-minute sessions per week. A workshop and uniform training program will be organized at SDM College of Physiotherapy, Dharwad, India for physiotherapists who will provide the assessment and the 2 intervention programs. This will be attended by [name] and [name] who will organize and coordinate the therapy program. The 2 intervention groups will be treated in all 4 locations limiting biases like contamination. The therapists conducting the assessments will be blinded to group assignment.

### Control Group Intervention

The control group (n=70) will receive the usual, comprehensive physical therapy for 45 minutes per session 3 times a week for 16 weeks. The therapy protocols will be individualized for every participant according to their level of impairment and preset goals, based on the principles of intensive repetitive task practice programs such as CIMT and HABIT. These consist of stretching of spastic muscles (activity-based dynamic stretching with child's active involvement to the spastic upper limb muscle, particularly muscles which are required for preparatory techniques will be involved in lengthening) and UE weight bearing exercises (ie, UE weight bearing in fundamental or functional position in the form of scapular and upper thoracic rotation and/or push and pull with a vestibular ball while maintaining corrected scapular positioning). A variety of arm and hand activities will be practiced, such as reaching for rings, removing and putting them back, ball throwing, opening a bottle cap, turning a door knob, clay activities, picking marbles from sand, and putting pellets and pegs into sockets, etc.

### Experimental Group Intervention

A typical session for the experimental group (n=70) will consist of stretching exercises followed by the game-based exercise program. Similar to the concept of “shaping,” and consistent with CIMT principles, CGR takes advantage of ergonomic properties of common objects to amplify limited and small amounts of voluntary movement and then allows opportunities for an appropriate switch to objects having more demanding movement requirements or functional demands. CGR allows object properties (size, weight, texture, and surface properties) to be easily manipulated in therapy. This provides graded practice for activities that need to be repeated in daily activities and in play. An important element of the platform is the ability to incorporate movement precision. In this regard, we target finger-hand function and not just transport and/or reaching movements.

Different computer games require different levels of movement amplitude, speeds, precision levels, as well as repetition and appeal to individual preferences. Furthermore, many inexpensive “off the shelf” computer games have a broad range of visuospatial cognitive content. Knowledge of the therapeutic value (object and games activities) can allow the therapist to prescribe an integrated program to target specific goals, for example, speed, accuracy, endurance, visuospatial functions, and cognitive inhibition, and to exercise 2 or 3 fingers, the whole hand, and bimanual tasks tailored to individual child abilities.

In a manner similar to interval training, 6 to 8 objects selected for specific therapy goals will be used to play computer games. Objects can be selected for motor skill training of finger/wrist or elbow and shoulder motions, and also of bimanual controls. Each object manipulation exercise will be used for 2 to 4 minutes. A number of possible objects which, when instrumented with the motion mouse, can be used for the game-based exercise program is shown in Figure 1 (see also [name] et al [31]). Many action and cognitive-type computer games are available to play; these will be selected by the treating therapist based on (1) degree of difficulty; (2) movement amplitude, speed, and accuracy; (3) visual-spatial processing requirement; and (4) personal preferences of the child. Common computer games that will be used in the game-based exercise program are shown in Textbox 1.

**Figure 1 figure1:**
[figure not shown]
Descriptions of the object manipulation tasks and their respective therapy values for assessment and/or treatment. A miniature, wireless motion mouse is attached with Velcro to each object. Each object manipulation task has specific fine or gross motor skill qualities for therapeutic exercise or ergonomic properties.

Computer games that will be used in the exercise program.Computer gameAqua Ball and Action Ball.Horizontal, single-axis brick buster with slow to moderate speed, and low to moderate movement precision.Small to moderate number of distracters and simple to complex 2D backgrounds.Jar of marbles and butterfly escape.Horizontal, single-axis matching colors with slow to moderate speed and low to moderate movement precision.Small to moderate number of distracters and simple and moving backgrounds.Owls and bubbles.A single-axis game that requires the player to move the mouse cursor on bubbles to pop them and free the owls to fly away.Hummingbird.A single-axis game that requires the player to move the bird up and down so that it touches the flowers.Feeding frenzy.Two-axis game play with slow motion element and low to moderate movement precision.Moderate to large number of distracters.

